#### Documentation of recruitment

The recruitment of the study sample will be documented in detail in order to judge the representativeness of included patients compared to the basic population of inpatients in depression treatment in the included study sites. Basic socio-demographic data and specific reasons for refusal of study participation of all screened patients and relatives, as well as exclusions of screened patients due to the above-mentioned exclusion criteria, will be closely documented. Therefore, a standardised operating protocol regarding the process of recruitment and informing patients as well as relatives has been developed.

#### Blinding

Due to the nature of the intervention, blinding of therapists and patient-relative tandems is not feasible. The primary outcome will be analysed by the study statistician, who will be blinded to the allocation of patients.

#### Control of intervention adherence

The intervention will be manualised and all related materials (e.g., slides, handouts) are standardised and will be provided by the leading study centre. Additionally, therapists will be trained in conducting the intervention within an intensive workshop to ensure process quality and standardisation of the intervention. Training success will be verified by using simulated therapy situations in the style of the Objective Structured Clinical Examination (OSCE). Only staff reaching a previously defined standard will be authorised to conduct the intervention within this trial. To further ensure the integrity of the intervention, the leading study centre will provide supervision as well as peer consultation via telephone or video conference. Finally, group sessions will be audiotaped and rated using self-developed scales [71] to judge the adherence and competence of therapists (T_Int_, intervention, c.f. Table 1).

#### Control of treatment-related confounders

As the intervention is compared to TAU, and the treatment of the patient is not restricted in any way in either condition, different types of treatment received by the patients might influence the effects. Therefore, data on treatment received after discharge will be gathered on both the patient and the relative level (c.f. Table 1) and their effects will be investigated using sensitivity analyses.

### Statistical methods

#### Analyses

The primary outcome, i.e., estimated DFDs one year after discharge from inpatient depression treatment, will be analysed by means of an analysis of covariance (ANCOVA) (independent variables: intervention, study centre; dependent variable: DFDs; covariate: severity of depressive symptoms at baseline) comparing the number of DFDs one year after discharge from inpatient depression treatment between the intervention and the control group. The primary analysis will be performed according to the intention-to-treat principle including all randomised patients. Multiple imputations will be used to account for missing data. Analyses with an alternative method of dealing with missing data and using available data will only be performed as sensitivity analyses in order to test the robustness of the findings. Secondary interval-scaled outcomes will be tested using t-tests and analyses of covariance (ANCOVA, if baseline measurement of the outcome is available). Dichotomous outcomes will be analysed using Fisher’s exact test, chi-square test (depending on expected cell frequencies), or logistic regression (if covariates are present). To ensure the interpretability of the results, each inferential statistical analysis will be accompanied by descriptive analysis. Differences in time until rehospitalisation will be analysed using Cox regression. For parameters in which the variance cannot be calculated analytically (e.g., cost-effectiveness), bootstrap methods will be used. Longitudinal analyses will be performed using general (interval-scaled outcome) or generalised (binary or ordered categorical outcome) linear mixed models. For the primary confirmatory analysis, a result with a type-I error under 5 % (*p* < .05) will be considered as statistically significant. Every additional analysis is seen as exploratory. Accordingly, a correction of the type-I error inflation will not be applied.

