### Intervention and control group

The intervention follows that of Shimazu et al. [17], but had to be modified in some aspects in order to fit with German conditions. The process of adaptation was based on the results of our own studies [13, 23, 27]. The PGIR will be conducted in a multifamily setting with one key relative per patient and the patient being absent. Groups will consist of three to five relatives. The PGIR consists of four group sessions, which will be conducted on a fortnightly basis. It will begin after discharge of the patient from inpatient depression treatment. Group sessions will be held by one therapist who possesses at least a Master’s degree or equivalent, and will last 90 to 120 min each. The intervention has two main components: Each group session consists of about 45 min of provision of information, while the remaining time is used for training problem-solving skills following the approach of Nezu et al. [28] as well as Hegel et al. [29]. The informational parts cover (1.) symptoms, epidemiology, course and prognosis of depressive disorders; (2.) support services for relatives as well as sources of personal strength and problem areas; (3.) cause of illness and (4.) treatment of depressive disorders. Problem-solving skill training is a brief intervention which has shown high efficacy in several diseases both in patients [30] and in relatives [31]. The PGIR aims to reduce caregiver burden and expressed emotion by teaching relatives how to systematically solve psychosocial problems. To evaluate the incremental effect of the intervention, the PGIR will be compared to treatment as usual (TAU), which in Germany mostly consists of psychotherapeutic and/or pharmacotherapeutic outpatient maintenance treatment provided by psychotherapists, psychiatrists or general practitioners [5]. In the intervention group, the only additional intervention to TAU will be the PGIR. In the control group, there will be no systematic information or psychoeducational intervention offered to relatives. To fit with routine care conditions, neither the inpatient treatment before discharge nor the patient treatment after discharge will be restricted in any way in the intervention group or the control group.

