#### Sample size calculation

The effect of the intervention in the study by Shimazu et al. [17] corresponds to an odds ratio of 0.09 (IG: 8 vs. CG: 50 % relapses), equivalent to a Cohen’s d of 1.33, which can be considered as a very large effect. However, the sample size was comparatively small, consisting of only 57 patient-relative tandems. Furthermore, there are some major differences to our study. First, the intervention in our study will be conducted by different therapists at several study sites. Second, our study is closer to routine conditions. Therefore, our study population will be more heterogeneous than in the study by Shimazu et al. [17]. A sample size of 128 patient-relative tandems one year after discharge (T_4_) is sufficient to detect a moderate effect of Cohen’s d = 0.50 (Cohen’s f = 0.25) with a power of 80 % by analysing the primary outcome via ANCOVA. In the study by Shimazu et al. [17], the dropout rate was about 5 %. As our study will be conducted under routine conditions, we estimate a conservative dropout rate of 10 % (*N* = 18) for the time of the intervention and a further 20 % lost to follow-up (*N* = 32). To reach a sample size of 128 patients under consideration of a total dropout rate of 30 %, a total of 180 patient-relative tandems shall be randomised.

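### The primary ANCOVA and the 128-tandem sample size leave out possible correlation within PGIR groups, which exists in the intervention arm only

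*Protocol article*

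**What the plan says.** The section on the intervention and control group describes the delivery. "Groups will consist of three to five relatives", and "Group sessions will be held by one therapist". Sessions are held "with one key relative per patient and the patient being absent", so the group members are relatives while the primary outcome, depression-free days (DFDs), is the patient's. On the other arm the article says: "In the control group, there will be no systematic information or psychoeducational intervention offered to relatives". Controls therefore have no comparable grouping.

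The Analyses section lists the terms of the confirmatory ANCOVA: "independent variables: intervention, study centre; dependent variable: DFDs; covariate: severity of depressive symptoms at baseline". It is run "according to the intention-to-treat principle including all randomised patients", with multiple imputation, and significance is declared for "a result with a type-I error under 5" per cent. Mixed models are named only for longitudinal analyses, and everything beyond the primary test is exploratory.

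The Sample size calculation section gives 128 tandems at twelve months for d = 0.50 and 80% power, "by analysing the primary outcome via ANCOVA", and 180 randomised. No ICC or design effect appears. The randomisation section recognises that a group format creates difficulties, but deals with them only through block sizes.

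**The concern.** This is a partially nested design: intervention patients are linked through their relatives' group and therapist, and control patients are not. If patients linked to the same group have more similar DFDs, the intervention-arm mean varies more than independent sampling implies. The centre term does not remove this. A centre main effect is common to both arms, whereas group variation sits in one arm and enters the treatment contrast directly.

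The trial has one confirmatory test at 5%. If the correlation is material, the planned interval for the DFD difference is too narrow and a borderline positive result is open to challenge. If the correlation is modelled, the test is valid but its power depends on an ICC that the sample size section does not mention.

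This is not detail left to an analysis plan. The article itself fixes the model terms and the basis of the sample size.

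**Working it through.** **Inputs from the article.** d = 0.50; 128 analysed, 1:1, so 64 per arm; alpha 5% (two-sided is assumed, as sidedness is not stated); group size 3 to 5; losses of 10% and then 20%, described as 30% in total.

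**Assumed.** ICC of 0.02 to 0.10, because the article gives none.

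**1. The plan's own figure.** With independent observations, noncentrality = 0.50 / √(1/64 + 1/64) = 2.83. The noncentral t with 126 df gives 80.1% power. For the randomised number, 128/0.70 = 183 and 128/(0.9 × 0.8) = 178, against 180 planned. So 128 reproduces with a design effect of 1 and no credit for the baseline covariate.

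**2. Clustering in one arm.** For m analysed patients per group, DE = 1 + (m − 1) × ICC in the intervention arm and 1 in the control arm. The variance of the contrast rises by the factor (DE + 1)/2.

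- Adjusted test: noncentrality = 0.50 / √((DE + 1)/64).
- Unadjusted test: type I error = 2 × [1 − Φ(1.96 / √((DE + 1)/2))].

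Example with m = 4, ICC = 0.10: DE = 1.30, variance factor 1.15, noncentrality 2.64, adjusted power 74.5%. The unadjusted critical value becomes 1.96/1.072 = 1.83, so the type I error is 6.8%.

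**3. Group size after dropout.** Sixty-four evaluable patients per arm already allows for dropout, so the groups should be thinned to match. Groups of 3 shrink to 3 × 0.70 = 2.1, and groups of 5 to 5 × 0.72 = 3.6.

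| Analysed group size | ICC | DE | Power, adjusted test | Type I error, unadjusted test |
|---|---|---|---|---|
| 2.1 | 0.02 | 1.022 | 79.7% | 5.1% |
| 2.1 | 0.05 | 1.055 | 79.1% | 5.3% |
| 2.1 | 0.10 | 1.11 | 78.0% | 5.6% |
| 3.6 | 0.02 | 1.052 | 79.1% | 5.3% |
| 3.6 | 0.05 | 1.13 | 77.6% | 5.8% |
| 3.6 | 0.10 | 1.26 | 75.2% | 6.5% |
| 4 (no loss) | 0.02 | 1.06 | 79.0% | 5.3% |
| 4 (no loss) | 0.05 | 1.15 | 77.3% | 5.9% |
| 4 (no loss) | 0.10 | 1.30 | 74.5% | 6.8% |
| 5 (no loss) | 0.02 | 1.08 | 78.6% | 5.5% |
| 5 (no loss) | 0.05 | 1.20 | 76.3% | 6.2% |
| 5 (no loss) | 0.10 | 1.40 | 72.7% | 7.4% |

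**4. Simulation of the planned ANCOVA.** Eight centres of 16 analysed patients, centre and baseline in the model, two groups of 4 per centre, 20,000 runs. Type I error was 4.9% at ICC 0, 5.8% at 0.05 and 6.9% at 0.10. The centre term therefore does not protect the test. At d = 0.50 the same unadjusted ANCOVA rejected in 79.1% (ICC 0.05) and 78.4% (ICC 0.10) of runs, so it keeps most of its rejection rate and pays in type I error instead.

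**5. The baseline covariate.** A baseline–DFD correlation r multiplies the variance by 1 − r². The article gives no r. For groups of 4, adjusted power is 81.0% at ICC 0.05 with r = 0.3. At ICC 0.10 it is 78.3% with r = 0.3 and 81.5% with r = 0.4.

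**The case against.** The case for leaving the plan alone has substance.

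- **The ICC may be small.** Patients do not attend, and the article calls the effect on them distal. Sessions are manualised, and therapists are tested and supervised. This favours the low end of the range. It does not make the ICC zero: the postulated mechanism carries changes in relatives through to the patient, so differences between groups could carry through too. The sponsor also rates therapist adherence and competence.
- **Some similarity cancels.** Tandems are randomised in batches within centre, so similarity due to ward or recruitment period is shared with controls from the same batch. In a simulation with an ICC of 0.05, type I error was 5.9% when all of the correlation was specific to the group and 5.2% when half was shared with batch controls.
- **The covariate may restore power.** This is true for plausible r. It does nothing for the type I error of the unadjusted test.

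A reader might infer that the p-value is certainly too small and that 80% power is certainly not delivered. The article does not support this, since both statements depend on an ICC that it does not give. A reader might also add a separate therapist correlation and reach a type I error of about 8%. The article does not say how many groups each therapist leads, so that structure would be invented, and a random effect for group alone would not address it.

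**Conclusion.** The point stands in conditional form. The stated confirmatory model and the sample size treat as independent patients who are linked by group in one arm. For any positive ICC specific to the intervention arm, the standard error is too small.

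Under an assumed ICC of 0.02 to 0.10, the planned test has a type I error of about 5.3% to 7% with typical intact groups. It is somewhat lower when dropout thins the groups, and the excess is negligible at an ICC of 0.02 or below. A valid group-adjusted test has about 75% to 80% power with 2.1 to 3.6 analysed patients per group. The 73% figure requires ICC 0.10 and every group intact at five. All of these power figures take no credit for the baseline covariate, which could bring power back to 80% or above.

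The two harms are alternatives, and adding them together would overstate the problem. Should be fixed; moderate confidence, because the size rests on an assumed ICC.

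**What to change.** Make the primary analysis a partially nested linear mixed model: fixed effects for arm, centre and baseline PHQ-9, a random effect for PGIR group in the intervention arm only, and a small-sample correction to the degrees of freedom. Analyse patients under the group to which their relative was assigned, so that the intention-to-treat set is unchanged. Keep the listed ANCOVA as a sensitivity analysis.

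In the sample size section, state the 80% as conditional on an ICC, an analysed group size and a baseline–DFD correlation, and show power over a range of each. No additional enrolment is proposed.

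The cost is wording in the protocol and analysis plan, settled before unblinded analysis. Group membership is known from delivery, so no new data are needed. The price is a slightly wider interval and a slightly lower stated power.

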### Measures taken to minimise/avoid bias

#### Randomisation and concealment of allocation

To control for known and unknown confounders and thus preclude selection bias, randomisation of patient-relative tandems will be conducted by means of a computer-based algorithm. Randomisation lists will adhere to a one-to-one study-group allocation ratio and will be stratified by centres with dynamically adaptable block sizes to prevent predictability and to ensure a balanced proportion of participants in both study conditions. To meet the challenges of a group intervention, randomisation blocks will include blocks with two, four, six, eight and ten patient-relative tandems. In each block size, the proportion of patient-relative tandems which will be allocated to the intervention or the control group is balanced. Once a study centre has recruited at least six patient-relative tandems, randomisation will be conducted with the appropriate block size. If a study centre has recruited two or four more patient-relative tandems before the first group session in the intervention group has taken place, they can be re-randomised and added to the PGIR and the control group. Randomisation lists will be centrally generated by the study statistician, who has no direct contact with clinicians or patient-relative tandems. To ensure allocation concealment, randomisation lists will be inaccessible to staff involved in the recruitment at the respective study centres. After recruitment of at least six patient-relative tandems (conducting the PGIR has to be feasible), study sites will report included patient-relative tandems to the leading study centre, which will report the allocation to the study sites as well as the patient-relative tandems. As the effect of the intervention was not moderated by any investigated variable in the study by Shimazu et al. [17], stratification for clinical characteristics will not be considered. However, central clinical variables (e.g., number of depressive episodes, duration of the current episode) will be gathered and their effects will be investigated in additional sensitivity analyses.

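### The t-tests, Fisher's exact and chi-square tests named for secondary outcomes without a baseline cannot account for centre, the stratification factor; the effect is small and conservative

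*Protocol article*

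**What the plan says.** All in the protocol article:

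- Primary model (Analyses): ANCOVA with "independent variables: intervention, study centre; dependent variable: DFDs; covariate: severity of depressive symptoms at baseline".
- Interval-scaled secondary outcomes (Analyses): "Secondary interval-scaled outcomes will be tested using t-tests and analyses of covariance (ANCOVA, if baseline measurement of the outcome is available".
- Dichotomous secondary outcomes (Analyses): Fisher's exact test, "chi-square test (depending on expected cell frequencies), or logistic regression (if covariates are present".
- Time to rehospitalisation (Analyses): "Differences in time until rehospitalisation will be analysed using Cox regression". No covariates or strata are listed or ruled out.
- Repeated measures (Analyses): "Longitudinal analyses will be performed using general (interval-scaled outcome) or generalised (binary or ordered categorical outcome) linear mixed models".
- Allocation (Randomisation and concealment of allocation): "Randomisation lists will adhere to a one-to-one study-group allocation ratio and will be stratified by centres". Severity is not a stratification factor: "stratification for clinical characteristics will not be considered".
- Timing (Table 1; Secondary outcomes, Patient level): rehospitalisation, patients' health care and medication use, and days of incapacity to work are measured at T1 to T4 only.

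Centre is named in the primary model and in none of the secondary analyses. All analyses other than the primary are labelled exploratory.

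**The concern.** The choice of test for a secondary outcome depends on whether that outcome has its own baseline, not on how patients were allocated. Days of incapacity to work therefore fall to a t-test, and rehospitalisation to Fisher's exact or chi-square unless covariates are brought in. None of these tests can carry centre.

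Allocation balanced within centre removes centre differences from the treatment comparison. An analysis that ignores centre still counts those differences as noise, so its standard error tends to be too large. The eight centres were deliberately chosen as different types of hospital, so differences in sick leave and readmission between them are plausible. The protocol itself calls rehospitalisation and incapacity to work objective indicators, which gives them weight in an unblinded trial with a self-rated primary outcome. Exploratory estimates are read mainly through their intervals, so those intervals should match the design.

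**Working it through.** **Inputs from the protocol article.** 128 analysable patients, d = 0.50, 80 % power (Sample size calculation); 5 % level (Analyses); eight centres (Study design); 1:1 allocation stratified by centre.

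**Assumptions, because the protocol gives no figures.** Two-sided test, outcome SD 1, 16 patients per centre split 8:8, centre explaining a share ICC of the variance, T0 severity explaining a share R².

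**1. The plan's own figure.** The exact two-sided t-test for d = 0.50 and 80 % power needs 63.8, so 64 per arm or 128 in total; power at 128 is 0.801. The figure reproduces. It is for the primary outcome. No secondary outcome has a sample size, so 128 and d = 0.50 serve here only as a scale.

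**2. Type I error of the t-test.** Centre effects cancel from the difference, so its true SD is √(4(1 − ICC)/128). The t-test uses the within-arm variance, which still contains centre: v = (1 − ICC) + ICC × (7/8) × (64/63), with SE = √(4v/128). The effective cut-off is 1.979 × SE/SD.

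| ICC | v | SE | true SD | SE/SD | cut-off | type I error (t, 126 df) | simulated (6000 runs) |
|---|---|---|---|---|---|---|---|
| 0.05 | 0.9944 | 0.1763 | 0.1723 | 1.023 | 2.025 | 4.5 % | 4.6 % |
| 0.10 | 0.9889 | 0.1758 | 0.1677 | 1.048 | 2.074 | 4.0 % | 3.9 % |

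At ICC 0.02 the simulated value is 5.0 %. Simulation error is √(0.05 × 0.95/6000) = 0.28 points.

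**3. Power for d = 0.50.** Simulated t-test against a linear model with centre and severity:

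| ICC | R² | t-test | adjusted | points lost |
|---|---|---|---|---|
| 0.02 | 0 | 0.808 | 0.807 | none |
| 0.05 | 0 | 0.815 | 0.820 | 0.5 |
| 0.10 | 0 | 0.814 | 0.838 | 2.4 |
| 0.05 | 0.10 | 0.804 | 0.858 | 5.4 |
| 0.05 | 0.25 | 0.803 | 0.913 | 11.0 |

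Closed-form check for centre alone, Φ(0.5/SD − cut-off):

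- ICC 0.05: Φ(2.902 − 2.025) = 0.810 against Φ(2.902 − 1.980) = 0.822, a loss of 1.2 points.
- ICC 0.10: Φ(2.982 − 2.074) = 0.818 against Φ(2.982 − 1.980) = 0.842, a loss of 2.4 points.

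**4. Severity: efficiency, not validity.** With R² of 0.10 or 0.25 the t-test's mean SE is 0.176 against a true SD of 0.172 to 0.174. That small gap comes from centre. Adjustment lowers the SE to √(4 × 0.85/128) = 0.163 and √(4 × 0.70/128) = 0.148. The unadjusted SE is honest about severity; it is simply larger than it need be.

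**5. Binary and time-to-event outcomes.** With no treatment effect and assumed centre SDs of 0.4 / 0.7 / 1.0 on the log scale (8000 trials each), chi-square rejects in 4.6 / 4.2 / 3.6 % of trials. A Cox model run without centre would reject in 3.9 / 2.9 / 2.3 %. With an assumed treatment effect, centre SD 0.4 and a severity effect (about 600 runs each), adjustment does not narrow the intervals:

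- Logistic: SE 0.413 unadjusted, 0.452 adjusted; power 0.53 and 0.58.
- Cox: SE 0.345 and 0.353; power 0.48 and 0.50.

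These SEs belong to different (marginal and conditional) effects. Any gain in power arises because the adjusted estimate is pulled less towards zero.

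**6. An opposing force.** The intervention is delivered in groups of three to five relatives. With an assumed therapy-group ICC of 0.05, groups of four and 29 % random dropout, the t-test's type I error is 5.2 / 4.9 / 4.4 % at centre ICC 0.05 / 0.10 / 0.20.

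**The case against.** The strongest reply is that a condensed article is silent on detail and that silence is not exclusion. For Cox regression, ANCOVA and logistic regression this stands. Each can contain centre, and a covariate list may sit in the analysis plan, which is not shown. A reader might infer that the Cox model ignores centre and severity; the text does not say so. The reply does not rescue the t-test, Fisher's exact test or ordinary chi-square test. Naming them is a stated choice, and they have no place for a stratum.

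Other points that stand:

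- Plain tests are not the whole secondary plan. Many secondary outcomes have a T0 value and go to ANCOVA, and mixed models are named for longitudinal analyses. Clinical variables and treatment received are to be examined in sensitivity analyses.
- A reader might infer that the error bars of all secondary outcomes are wrong and too wide. That is not supported. Severity was not stratified, so omitting it does not invalidate the t-test. For logistic and Cox models adjustment need not narrow the interval. Clustering by therapy group can offset the conservatism.
- A reader might infer that the economic evaluation inherits the problem. The Analyses section assigns cost-effectiveness to bootstrap methods, so these tests do not feed it.
- With few events, seven centre terms plus covariates may overload a logistic model. Choosing the test by expected cell counts is reasonable for sparse data, so the remedy must allow for that.

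**Conclusion.** The point holds in a limited form. For secondary outcomes without a baseline, the named t-tests, Fisher's exact and chi-square tests cannot reflect the centre stratification that the design uses and the primary analysis respects. Taking centre alone, the t-test is mildly conservative: type I error about 4 to 4.6 %, with 0.5 to 2.4 points of power lost, if centre explains 5 to 10 % of variance. At 2 % the effect vanishes. Omitting T0 PHQ-9 as well brings the total loss to about 5 to 11 points if it explains 10 to 25 % of variance at centre ICC 0.05; the severity part is lost efficiency, not an invalid test.

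Every centre and severity effect here is assumed, as are equal centres and exact within-centre balance at analysis. Priority is low: the error from omitting centre is in the safe direction, these analyses are exploratory, and the one confirmatory test already adjusts for both variables. It is still worth correcting, because the improvement needs no new data.

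**What to change.** Add one statement to the analysis plan: secondary between-group analyses account for centre as the primary analysis does.

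- Interval-scaled outcomes: linear model with centre.
- Dichotomous outcomes: logistic regression with centre, or Mantel-Haenszel by centre when events are sparse.
- Time to rehospitalisation: Cox regression stratified by centre. This is a clarification, since the present sentence does not exclude it.
- Outcomes without their own baseline: T0 PHQ-9 as covariate where the number of events allows it.
- Unadjusted t-tests, Fisher's exact and chi-square tests may stay as descriptive or sensitivity analyses.

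The cost is wording only. Centre and T0 PHQ-9 are already recorded for the primary analysis, and the sample size does not change.
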